## Abstract

**Background:**

Current evidence suggests that good quality sleep is associated with preserved cognitive function and reduced dementia risk in older adults. Sleep complaints are especially common among older adults with mild cognitive impairment (MCI), and this may contribute to their increased risk for progression to dementia. Thus, improving their sleep may be important for maintaining their cognitive health. Chronotherapy is a set of intervention strategies that can improve sleep quality through strengthening the entrainment of the biological clock to the solar light-dark cycle, and includes strategies such as (1) bright light therapy (BLT); (2) physical activity (PA); and (3) good sleep hygiene. Of these strategies, BLT is the most potent and is based on providing individualized timing to entrain circadian rhythms. Thus, a personalized chronotherapy intervention of individually timed BLT and individually tailored PA promotion, in conjunction with general sleep hygiene education may promote older adult sleep quality. We therefore aim to carry out a proof-of-concept randomized controlled trial (RCT) to examine the efficacy of such a personalized chronotherapy intervention to improve sleep quality among older adults with MCI.

**Methods/design:**

This was a 24-week RCT of a personalized chronotherapy intervention aimed to primarily improve sleep quality as measured by the MotionWatch8©. Participants in the personalized chronotherapy group (INT) will receive four once-weekly, general sleep hygiene education classes, followed by 20 weeks of (1) individually timed BLT and (2) bi-weekly, individually tailored PA counseling phone calls in conjunction with receiving a consumer-available PA tracker—the Fitbit® Flex™. Ninety-six adults (aged 65–85 years) classified as having MCI (i.e., Mini-Mental State Exam (MMSE) ≥ 24; Montreal Cognitive Assessment (MoCA) ≤ 26; without dementia or significant functional impairment) will be randomized to either INT or a waitlist control group (CON).

**Discussion:**

The results of this trial will help determine if a personalized chronotherapy intervention that includes individually timed BLT and individually tailored PA promotion, along with general sleep hygiene education can promote sleep quality among older adults at increased risk for dementia. Our results will help inform best practices for promoting sleep quality among older adults with MCI.

**Trial registration:**

ClinicalTrials.gov, NCT02926157. Registered on 6 October 2016.

## Background

Worldwide, there is one new case of dementia detected every 4 s [1] and the costs of treating this epidemic are staggering. As of 2015 the estimated worldwide costs for dementia treatment were US$818 billion, and in 2018 the costs are expected to balloon to over US$1 trillion [2]. There is not yet a cure for dementia, and thus intervening with lifestyle strategies on known risk factors for cognitive impairment is an important strategy for reducing dementia risk—or at least delaying its onset [3].

Older adults with mild cognitive impairment (MCI) are at increased risk for dementia [4]. MCI is a clinical entity characterized by cognitive decline greater than expected for an individual’s age and education level, but which does not interfere notably with everyday function [5]. Importantly, 30% of older adults diagnosed with MCI develop dementia within 5 years [6], while in the same 5-year timespan only 2% of older adults without MCI are diagnosed with dementia [7]. There is currently a lack of effective pharmaceutical options for treating MCI, and thus lifestyle modifications to reshape the cognitive trajectory of older adults with MCI are an important line of scientific inquiry [8].

Improving older adult sleep quality is a promising strategy for maintaining older adult cognitive health. More than half of adults over 65 years report at least one chronic sleep complaint—the most common being the inability to stay asleep at night [9]. Poor sleep quality is also an important risk factor for Alzheimer’s disease (the most common form of dementia) [10], and older adults with MCI are more likely to experience poor sleep quality than healthy older adults [11]. Moreover, epidemiological evidence suggests poor sleep quality is associated with an increased risk of conversion from MCI to dementia [12], and thus improving sleep quality among individuals with MCI may help reduce dementia risk.

Sleep quality is closely tied to the function of circadian rhythms (i.e., ~ 24-h biological clock [13]), which coordinates physiology and behavior with the solar light-dark cycle [14–16]. Briefly, the process by which the biological clock is synchronized with the solar light-dark cycle is known as *entrainment* [17], and is regulated by the activity of the suprachiasmatic nuclei (SCN) which serves as “the master biological clock” of the central nervous system [18]. This process of entrainment occurs through certain external stimuli, known as *zeitgebers* (from the German *time-givers*), and helps to prevent inadvertent drifting or divergence from the 24-h day [19]. Of particular importance, aging is associated with (1) the biological clock initiating sleep-promoting mechanisms earlier in the day [20, 21]; and (2) decreased amplitude in circadian signals that increase sleep need [22, 23]. The weakening of circadian regulation that occurs with aging likely plays a prominent role in the fragmentation of sleep-wake rhythms observed in older adults during (1) the wake maintenance zone, which occurs 2–3 h before habitual bedtime and (2) the sleep maintenance zone, which occurs 2–3 h before habitual wake time [24]. Because aging appears to be linked to the divergence of the biological clock, chronotherapies that use effectively timed zeitgebers to help strengthen the entrainment of the SCN to the solar light-dark cycle may improve older adult sleep quality [25].

The principal entraining zeitgeber for the human biological clock is light [25, 26], which exerts its influence on blue-light-sensitive receptors in the retina [27]. Retinal light exposure directly stimulates greater activity of the SCN, which *phase delays* the biological clock such that the desire for sleep decreases and wakefulness increases (or is maintained); reduced retinal light exposure results in less activity of the SCN and increases the desire to sleep by *phase advancing* the biological clock [17]. While the importance of light is thus integral for the proper function of the SCN and the biological clock, older adults have reduced sensitivity to light, which leads to poorer function of the SCN and divergence of the biological clock from the solar light-dark cycle [28]. Behavioral changes in older adulthood—such as spending less time outdoors—could also further decrease bright light exposure, which may be a key factor in decreased amplitude of circadian rhythms [24]. Thus, older adults in particular may benefit from effectively timed bright light to strengthen the entrainment of the SCN to the solar light-dark cycle.

Bright light therapy (BLT) is an increasingly popular chronotherapy strategy [24]. While the efficacy of BLT as an intervention strategy is currently inconclusive [29, 30], the biological clock is not equally amenable to shifts at each phase in the circadian rhythm [17]. Indeed, any zeitgeber can cause the biological clock to phase advance, phase delay, or be entirely phase neutral depending on the biological clock time at which a zeitgeber is administered. As such, successful BLT requires an individualized approach where proper timing is essential [24].

Another potential zeitgeber for use as chronotherapy is physical activity (PA) [28, 31, 32]. Briefly, PA performed in the morning or early afternoon does not appear to have a consistent effect on phase shifts of the biological clock; however, engaging in PA in the late afternoon causes a phase advance of the biological clock, while late night PA causes phase delay of the biological clock [31, 32]. The time-based response to how PA can impact the SCN is hypothesized to coincide with the timing of the opening of the “sleep gate”—the shift of the biological clock from generating a waking signal that reduces sleep need, to generating a signal that facilitates sleep [33].

However, the use of PA in chronotherapy is challenging. The current evidence describing the effects of PA as a zeitgeber comes from controlled laboratory experiments, where the timing and intensity of PA in the form of exercise is tightly controlled. Conducting an intervention where participants would be asked to engage in regularly timed PA at a prescribed intensity would (1) be burdensome to participants and (2) require enormous resources to ensure participant adherence. More importantly, evidence suggests that regular PA—regardless of timing—is associated with better sleep quality [34, 35]. Less than 5% of older adults meet the current guidelines of 150 min/week of PA [36], and older adults with MCI are less active than their cognitively healthy peers [37]. Given that individually-timed BLT appears to be the most powerful chronotherapeutic [24], promoting older adult PA in conjunction with BLT may be a feasible approach to providing personalized chronotherapy.

In addition to the potential benefit of combining individually timed BLT with PA, improving sleep hygiene can positively impact sleep quality and aid chronotherapy [38]. Poor sleep hygiene exacerbates or even causes poor sleep, whereas good sleep hygiene results in feeling more rested and alert upon awakening—as well as a greater ability to function throughout the day. Sleep hygiene education, which teaches behavioral strategies to promote healthy sleep (e.g., avoiding watching television before bed), can also be useful as a strategy to promote behaviors which may improve circadian regulation—including light exposure and PA [39]. Current recommendations for improving older adult sleep quality therefore suggest combining (1) BLT; (2) PA; and (3) sleep hygiene education [40]. Importantly, preliminary evidence suggests combined BLT and PA in the form of exercise training, and sleep hygiene can improve sleep quality in older adults with insomnia [41].

While these results are promising, there remains a gap in our understanding of whether personalized chronotherapy is an effective approach to improving sleep quality among older adults with MCI. Thus, we propose a proof-of-concept randomized controlled trial (RCT) to examine the efficacy of a personalized chronotherapy intervention combining (1) individually timed BLT; (2) individually tailored PA promotion; and (3) general sleep hygiene education to improve the sleep quality of older adults with MCI. We will use a multimodal personalized chronotherapy intervention for improving the sleep quality of older adults with MCI, which may ultimately help in maintaining cognitive function and reduce dementia risk in this population.

## Methods

### Design

We propose a proof-of-concept RCT of 96 community-dwelling older adults with MCI, aged 65 to 85 years. Participants randomized to the personalized chronotherapy group (INT) will receive the intervention over a 24-week period. There will be three measurement sessions with monthly monitoring (Fig. 1). Briefly, at each monthly monitoring participants will complete by telephone (1) the EuroQol 5D (EQ5D), a standardized instrument for measuring generic health status [42] and (2) the ICECAP index of capability for older people, which examines older adult quality of life [43]. Ethical approval has been obtained from the University of British Columbia's Clinical Research Ethics Board (H16-01029, 22 September 2016). All participants will provide a personally signed and dated informed consent document indicating that the individual has been informed of all pertinent aspects of the trial.

**Fig. 1 Fig1:**
[figure not shown]
Standard protocol items: recommendation for interventional trials (SPIRIT) figure

### Recruitment

We will recruit from the community and from our own database of individuals who have consented to be contacted about future research. Briefly, participants who have been previously involved in our research and have consented to being contacted about future research will be contacted. In addition, we will recruit participants by advertisements placed in local community centers, newspapers, and word-of-mouth referrals. Interested individuals will first be screened by telephone to check for general eligibility according to our criteria, and then screened using the Physical Activity Readiness Questionnaire (PAR-Q) [44]. Briefly, the PAR-Q is a simple screening tool for determining readiness to begin a PA program and for uncovering any potential health risks that may be associated with an increase in PA. Those who appear eligible will attend an information session.

### Eligibility

#### Inclusion criteria

We will include community-dwelling men and women who (1) are aged between 65 and 85 years and are living in their own home; (2) have preserved general cognition as indicated by a Mini-Mental State Examination (MMSE [45]) score ≥ 24/30; (3) have a baseline Montreal Cognitive Assessment (MoCA [46]) score < 26/30; (4) do not have dementia of any type; (5) do not have any significant impairment in daily function; (6) are currently experiencing poor sleep quality as indicated by a Pittsburgh Sleep Quality Index (PSQI [47]) score > 5; (7) scored < 5/15 on the 15-item Geriatric Depression Scale [48, 49]; (8) are able to walk independently and are in sufficient health to participate in regular PA as indicated by the PAR-Q [44]; and (9) understand, speak, and read English with acceptable visual and auditory acuity.

#### Exclusion criteria

We will exclude individuals who are (1) diagnosed with obstructive sleep apnea; (2) receiving continuous positive air pressure (CPAP) treatment; (3) at high risk for cardiac complications during PA or unable to self-regulate activity or to understand recommended PA level; and (4) have clinically important peripheral neuropathy or severe musculoskeletal or joint disease that impairs mobility.

### Sample size calculation

Our primary outcome measure is sleep efficiency as measured by the MotionWatch8© wrist-worn actigraphy unit (MW8) (CamNtech; Cambridge, UK) [50]. Sleep efficiency is one of several validated objective sleep parameters [51], and it is the gold standard in evaluating insomnia treatment efficiency [52]. Our pilot data suggested that sleep hygiene education alone had a small effect on sleep efficiency after 6 months (*d* = 0.16). As the proposed INT program is multifaceted (i.e., sleep hygiene education + individually timed BLT + individually tailored PA counseling), we anticipate a larger effect size in this RCT. Thus, assuming a two-sided alpha of 0.05, correlation across adjacent time points of 0.88 (estimated from pilot data), 40 participants per group will provide power of 0.85 to detect an effect size of 0.50 at the end of the intervention [53]. To allow for a drop-out rate of 15%, we will recruit a total of 96 older adults (i.e., 48 per group).

### Measurements

Baseline measurements will be obtained prior to randomization. There will be three measurement sessions: baseline, 12 weeks, and 24 weeks.

#### Descriptors

We will measure height using a wall-mounted stadiometer and measure weight using a calibrated digital scale. General health and socioeconomic status will be ascertained by questionnaire. In addition, we will survey participants at baseline for obstructive sleep apnea risk using the Snoring, Tiredness, Observed apnea, Blood pressure, Body mass index, Age, Neck circumference and Gender (STOP-BANG) questionnaire [54].

#### Primary outcome

We will measure sleep efficiency using the MW8. Briefly, the MW8 is a uni-axial, lightweight, wrist-worn accelerometer designed to observe acceleration ranging in magnitude from 0.01 to 8 G, with a frequency of 3–11 Hz. The filtered acceleration signal is digitized and the magnitude is summed over a user-specified time interval, or “epoch”. At the end of each interval, the summed value or activity “count” is stored in memory and the integrator is reset. Estimates of sleep quality parameters can then be extracted from the device based on the number of counts for a given epoch. For the present study, we will use 60-s epochs, which is consistent with current guidelines for estimating sleep quality [55].

Participants will first be fitted with the MW8 on the non-dominant wrist and provided detailed information on its features (i.e., the light sensor, event marker button, and status indicator). Participants will be instructed to press the event marker button each night when they start trying to sleep, and again each morning when they are finished trying to sleep. We will also provide participants with the Consensus Sleep Diary (CSD)—which they will be asked to complete upon awakening each morning [56]. After wearing the MW8 continuously for at least 14 days, participants will return the MW8 and completed CSD. We will subsequently download and analyze the MW8 data using MotionWare software 1.0.27 (CamNtech). The responses from the CSD will be used to confirm sleep windows identified by participants (as determined by time-stamped event markers). In cases where the event marker and CSD entries disagree for the start time of the sleep window, we will use the light sensor data to determine “lights out”. Similarly, when the event marker and CSD entry disagree for the end of the sleep window, we will use “lights on” and activity onset to determine the end of the sleep window. The MotionWare software will be used to estimate sleep efficiency (i.e., time asleep expressed as a percentage of time in bed).

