#### Allocation concealment

Recruitment and enrollment of participants will be managed by the research coordinator who will screen for study eligibility, obtain informed consent, and conduct baseline assessment. Following completion of baseline assessment, the research coordinator will access the web-based randomization service and the participant will be assigned a participant number and allocated to the INT or the CON group. Research personnel performing the outcome assessment and data analysis will be blinded to group allocation. We will not be able to blind participants or personnel delivering the interventions to group allocation.

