##### Individually timed bright light therapy (BLT)

In week 5, participants in the INT group will meet with a trained research assistant to develop a daily BLT schedule designed to improve sleep quality and address sleep complaints. Using the results from the STOP-BANG questionnaire, we will first counsel participants with moderate-to-high risk of sleep apnea to see a physician. The participant will then work with the research assistant to determine the best regularly scheduled bed time and wake time in order for the participant to dedicate 8 h to sleeping each night (i.e., sleep window). Using the results from the MW8 sleep recordings (i.e., the participant’s current sleep window), and the participant’s recommended sleep window, we will classify participants as (1) phase advanced (falls asleep earlier than intended); (2) phase delayed (falls asleep later than intended or wakes up later than intended); or (3) phase neutral (falls asleep when intended). Participants will then be provided with a commercially available BLT device (Philips goLITE BLU) and be provided a personalized BLT schedule based on their phase classification. The goLITE BLU emits short-wave blue light (~ 200 lx), which possesses greater phase-shifting properties than the rest of the visible light spectrum [61–64]. All BLT doses will be 1 h in duration, twice daily for 20 weeks (i.e., week 5–24). The time and dose-dependent effects of BLT have been well-described elsewhere [65–69].

**Phase advanced:** Participants will be counseled to use BLT 2 h after waking, and again 11 h later (e.g., morning BLT dose, 8:00–9:00 a.m.; evening BLT dose, 7:00–8:00 p.m.). Participants will be instructed to avoid light 1.5 h before sleep window onset. Participants can otherwise continue their normal light routine at night.

**Phase delayed:** Participants will be counseled to use BLT 30 min after waking, and again 11 h later. Participants will be counseled to avoid all light 3 h before sleep window onset.

**Phase neutral:** participants with a neutral sleep phase will be further sub-categorized based on their current waking routine.

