Participants who wake up earlier than intended will be counseled to use BLT 2 h after waking, and again 11 h later. Participants will be counseled to avoid light 1.5 h before sleep window onset. Participants can otherwise continue their normal light routine at night.Participants who wake up when intended will be counseled to use BLT 1 h after waking, and again 11 h later. Participants will be instructed to avoid light beginning 2 h before sleep window onset. Participants can otherwise continue their normal light routine at night.

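### The light-sensor tie-break for the start of the sleep window is not independent of arm, because only INT is told to avoid light before bed; it can bias sleep efficiency and sleep latency on disputed follow-up nights.

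*Protocol article*

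**What the plan says.** - **Outcome.** The primary outcome is actigraphic sleep efficiency, defined under Primary outcome as "time asleep expressed as a percentage of time in bed". The start of the window therefore enters the denominator.
- **Window start.** The event marker comes first and the diary is used to confirm it. Only if they disagree does the light sensor decide: "for the start time of the sleep window, we will use the light sensor data to determine" lights out. For a disputed window end, the article uses lights on together with activity onset. For the start it names light alone.
- **Sleep latency.** Under Objective sleep quality, latency is counted from lights out.
- **Light instructions, INT only.** Under Individually timed bright light therapy (BLT), phase-delayed participants receive this instruction: "Participants will be counseled to avoid all light 3 h before sleep window onset". For phase-neutral participants who wake when intended it is: "Participants will be instructed to avoid light beginning 2 h before sleep window onset". The phase-advanced and the early-waking phase-neutral groups are given 1.5 h. The INT sleep hygiene classes also teach avoiding light at night.
- **CON.** Under Waitlist group (CON), there is no intervention in weeks 5–24 and usual activity continues.
- **Timing.** Recordings are made at baseline, 12 and 24 weeks, with at least 14 days of wear. The light programme runs in weeks 5–24.
- **Blinding.** Under Allocation concealment: "Research personnel performing the outcome assessment and data analysis will be blinded to group allocation".

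**The concern.** The tie-break relies on a signal that the intervention deliberately changes, in one arm and only after baseline. On a disputed INT night the light trace may go dark well before the person tries to sleep. If that darkening is read as lights out, the window starts too early and the denominator of sleep efficiency grows. CON has no matching mechanism.

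An error of this kind is not removed by having a baseline measurement. The planned mixed model, with group, time and their interaction, would attribute it to the intervention. Sleep latency shares the problem because it starts at the same point.

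There is also a blinding question. Whoever settles a disputed night reads the light record, which in INT may show two one-hour light sessions a day and dim evenings. That person would be making a judgement that moves the primary outcome while possibly able to infer the arm.

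**Working it through.** **Plan figures.** The article gives no figure for how often, or by how much, the tie-break moves the window, so there is none to reproduce on this point. The design figures used below as a yardstick do reproduce:
- Recruitment: 40 / (1 − 0.15) = 47.1, rounded up to 48 per group, 96 in total, as stated.
- Power: a 2-df group-by-time test over three visits, with AR(1) correlation 0.88, differences of 0, 0.25 and 0.50 SD and 40 per group, gives 0.855 against the stated 0.85. The article does not name its formula, so this match assumes linear growth of the effect. The point does not depend on it.

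**Step 1. Could darkening precede bedtime in INT?** Assume waking at the end of an 8-h window, so the next window starts 16 h after waking. The second light session starts 11 h after the first and lasts 1 h.

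| INT class | Evening session ends (h after waking) | Light avoidance starts (h after waking) |
|---|---|---|
| Phase advanced, or neutral and waking early | 2 + 11 + 1 = 14 | 16 − 1.5 = 14.5 |
| Phase delayed | 0.5 + 11 + 1 = 12.5 | 16 − 3 = 13 |
| Neutral, waking when intended | 1 + 11 + 1 = 13 | 16 − 2 = 14 |

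In each class the light session ends 0.5–1 h before avoidance begins. A participant who follows the schedule could thus show a bright-to-dark step 1.5–3 h before bed.

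**Step 2. Shift on one affected night.** Let SE be the true efficiency, L the minutes wrongly added to the window, and q the share of L scored as sleep. The 480 min is the 8-h planned window. SE = 80% is an assumption, since the article gives no value.

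Shift = (SE × 480 + q × L) / (480 + L) − SE

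| L (min) | q = 0 | q = 0.5 | q = 0.8 | q = 1 |
|---|---|---|---|---|
| 90 | 384/570 = 67.4%, −12.6 | −4.7 | 0 | +3.2 |
| 120 | 384/600 = 64.0%, −16.0 | −6.0 | 0 | +4.0 |
| 180 | 384/660 = 58.2%, −21.8 | −8.2 | 0 | +5.5 |

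Shifts are in percentage points. The sign depends on whether quiet time in the dark is scored as sleep at a lower or higher rate than the night itself.

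**Step 3. Average over nights, q = 0.** Multiply by the share of nights affected (assumed):
- L = 90: −0.6, −1.3 and −2.5 points at 5%, 10% and 20%.
- L = 180: −1.1, −2.2 and −4.4 points at 5%, 10% and 20%.

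**Step 4. Against the target effect.** No SD is given. At an assumed SD of 8 points, d = 0.50 equals 4 points, and a 1.3-point shift leaves d = 0.50 − 1.3/8 = 0.34. For SDs of 6 to 10 points, the remaining d is 0.28 to 0.37. On a baseline-to-24-week change test with AR(1) correlation, power is 0.915 without the shift and about 0.61 with it (0.47 to 0.69 over the same SDs). This is not the test that reproduces 0.85, and it supposes that the shift is present at 24 weeks.

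**Step 5. Latency.** With q = 0 and L = 90, latency rises by 90 min on an affected night, or 0.10 × 90 = 9 min on average at 10% of nights.

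**The case against.** The strongest reply is that the rule is a limited fallback and an objective one. It applies only when two self-reports conflict. The article gives neither the share of such nights nor the way lights out is read from the trace; a threshold and a definition of disagreement belong in a scoring manual, and their absence from an article is no finding. If light merely adjudicates between the marker time and the diary time, the error cannot exceed the gap between them, which may be minutes. Sleep is scored from movement, so quiet time in the dark could count as sleep and push the shift to zero or above. Nothing says who scores the windows, what they see, or whether a wrist sensor shows a lamp of about 200 lx distinctly.

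Much of this stands. A reader might infer that the rule sets sleep onset from light, or that it does bias sleep efficiency against INT by several points. The article supports neither. The rule fixes the start of the window, not the onset of sleep. The larger losses need full compliance with light avoidance, its start read as lights out, and no added time scored as sleep; an average of 4.4 points also needs 20% of nights affected by 3 h each. Exposure is clear only at 12 weeks, because the article does not say whether the 24-week recording is worn before or after the light programme ends.

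It does not remove the dependence itself: the stated fallback uses a signal that differs by arm by design, with no stated activity check at the window start.

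**Conclusion.** The point holds as a risk created by two stated rules taken together. On disputed follow-up nights the tie-break can misplace the window start differently in INT and CON, and so bias sleep efficiency and sleep latency. The likelier direction is a longer window and lower efficiency in INT, which could hide part of a real benefit.

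Size and direction cannot be determined from the article. The figures of 12.6 points per affected night and 1.3 points on average illustrate one case: 80% efficiency, 480 min, 90 min misplaced, no added sleep scored, 10% of nights affected. The shift is zero if lights out is read correctly, and zero or reversed if enough of the added time is scored as sleep. A conclusion that the trial will understate the effect, or wrongly show harm, would go beyond the text.

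On blinding, the light record may reveal allocation to the scorer, at odds with the stated blinding. The article does not show that it will.

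**What to change.** For the primary analysis, resolve disputed window starts by a fixed order that does not use light: the event marker if present, otherwise the diary time of starting to try to sleep. Apply it identically in both arms and at all three visits, and hide the light channel from the person scoring the windows.

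Keep the light-based window as a sensitivity analysis, add one that excludes disputed nights, and report the number of disputed nights by arm and visit. That count would show how much the rule can matter.

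The cost is a change to the scoring rules and rescoring of disputed nights already recorded. At 1 October 2017 the article reports 38 of 96 participants recruited, and the marker and diary data are already part of the planned collection. The downside is that these nights then rest on self-report by unblinded participants, and INT participants work out a scheduled bed time with the research assistant, so the new order is not wholly immune to the intervention either. It removes the direct dependence on light. No change to the light instructions is implied.
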